**Discussion:**

This study will be a standardized, scientific, clinical trial designed to evaluate the therapeutic effects and safety of DQS and HA for diabetic dry eye treatment.

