### Trial design {8}

This is a prospective, randomized, triple-blind, exploratory, controlled trial design study. Participants will be randomized (1:1) to the DQS group (*n* = 101) or HA group (*n* = 101). Participants in the DQS group will be administered one drop six times per day for 8 weeks (56 days), while the participants in the HA group will receive the assigned treatment over an 8-week period, one drop six times per day as depicted in Fig. 1.

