### Statistical methods

#### Statistical methods for primary and secondary outcomes {20a}

In this research, unless otherwise mentioned, the significance level is set to 5% two-sided and the confidence coefficient is set to 95%. The demographic data of the study’s subjects will be tabulated by calculating the mean and standard deviation for continuous variables and the frequency and percentage for categorical variables. If the continuous variables do not follow a normal distribution, they will be converted appropriately by logarithmic transformation or other means and aggregated with the mean and standard deviation, or the median and interquartile range will be utilized as descriptive statistics.

The safety analysis will be conducted based on a safety analysis population that includes subjects who have received at least one dose of medication after randomization.

Data will be collected for all patients participating in the treatment at the following stages: baseline, first follow-up at week 4 (day 28), and second follow-up at week 8 (day 56 ). The primary outcome measures for this study are NITBUT scores before and after treatment. For the main endpoint, between-group comparisons using baseline as a covariate and an analysis of covariance will be done to produce the adjusted mean, its 95% confidence interval, and the *p*-value. A paired *t*-test will be used to make within-group comparisons. To ensure participant safety, frequencies and proportions will be computed for each group and item, and comparisons between groups will be made using Fisher’s exact probability test or the *χ*^2^ statistic.

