#### Adverse event reporting and harms {22}

Due to the low-risk nature of the trial, no AEs are anticipated. For very rare cases such as eye secretion, eye irritation, eye itching, congestion, and eye pain, HESH Certified Review Board will be notified; experimental treatments will be discontinued promptly, and professional ophthalmologist will provide treatment .

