## Discussion

DM is a complex metabolic disorder and several mechanisms have been speculated for the cause of DE in DM patients. Some suggest that insulin is necessary for the proliferation of acinar lacrimal gland and cornea epithelial cells [30], while others propose that the tear reflex is weakened owing to diabetic corneal neuropathy-induced corneal insensitivity [31]. Additionally, it has been shown that the amount of glucose and advanced glycation end-products (AGEs) might rise in tears, promoting hyperosmolarity and inflammation [32].

Prior studies have shown that DM increases the risk of developing chronic DED [33, 34] due to tear protein alteration, decreased corneal sensitivity, and lower reflex-induced tear secretion [35]. Manaviat et al. [36] observed that the prevalence of DED in type 2 diabetic patients was 54.3% and that the rate of morbidity was significantly greater than in non-diabetic controls. In addition, they discovered that DED was substantially linked with age, gender, diabetes duration, and diabetic retinopathy. Studies conducted by Najafi et al. [37] and Zou et al. [34] suggest that glycosylated hemoglobin (HbA1c) levels had an association with diabetic DED.

DQS stimulates P2Y2 receptors on the ocular surface, which enhances the secretion of water and secretory mucin from conjunctival tissue. Therefore, tear film stability and quality can be improved [38]. However, the effect of DQS on the tear film of DM humans has not been previously assessed. This result should allow us to compare the clinical efficacy and safety of 3% DQS in diabetic patients with DED and provide clinicians with more treatment options. On the other hand, HA is a glycosaminoglycan, and with its sponge-like structure of polysaccharide chains, it can bind with water and acts as a reservoir for slowly releasing water molecules [39]. As a result, HA eye drops are commonly used to treat DED, while initial findings from a pilot study suggest that HA eye drops can improve signs and symptoms of diabetic DE [40]. The possible benefits exhibited by the two topical ophthalmic eyedrops will be related to corneal epithelial recovery and secretion and not changes in the underlying pathology created due to DM.

However, a large RCT has not been conducted to understand the benefits of HA eye drops on diabetic DED patients.

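### The only between-group safety comparison named is a Fisher or chi-square test, which says little at the event rates the protocol expects; risk differences with 95% confidence intervals should take its place

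*Protocol article*

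**What the plan says.** The abstract describes the trial as "designed to evaluate the therapeutic effects and safety of DQS and HA for diabetic dry eye treatment". The main Discussion expects the result to let clinicians "compare the clinical efficacy and safety of 3% DQS in diabetic patients with DED".

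Statistical methods {20a} contains the safety analysis:

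- The population is a "safety analysis population that includes subjects who have received at least one dose of medication after randomization".
- In it, "frequencies and proportions will be computed for each group and item, and comparisons between groups will be made using Fisher’s exact probability test" or, alternatively, a chi-square test.
- The general default for the research is that "the significance level is set to 5% two-sided and the confidence coefficient is set to 95" per cent.
- For the primary endpoint, the same section plans an adjusted mean with its 95% confidence interval and a p-value. It names no between-group estimate or interval for adverse events.

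On how often events are expected, Adverse event reporting and harms {22} says: "Due to the low-risk nature of the trial, no AEs are anticipated". It then introduces the ocular events with "For very rare cases such as eye secretion, eye irritation, eye itching, congestion, and eye pain", and section {11b} uses the same description. No numeric rate is given anywhere. Sample size {14} rests on NITBUT alone and states no safety margin or detectable excess.

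**The concern.** A significance test asks whether the data rule out equal event rates. When few events are expected, it will seldom do so even if the rates really differ. The article expects very few events, yet the test is its only named way of setting one arm against the other.

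If the results follow this plan literally, the between-group safety result will probably be a column of p-values above 0.05. Such a column does not tell the reader how large an excess of ocular events on either drop is still compatible with the data. That is what a clinician choosing between the two drops needs from the promised comparison.

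**Working it through.** **Inputs.** Arm size is 101, from Trial design {8}. The level is 0.05 two-sided, from {20a}. The tests are Fisher's exact or chi-square, from {20a}. Event rates are not in the documents, so those below are assumptions and are shown as a range. The protocol states no safety figure that could be reproduced first.

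**Step 1: the smallest significant split.** With *a* events in one arm and 0 in the other, n = 101 each, the two-sided Fisher p-value is 2 × C(101, a) / C(202, a).

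- a = 5: 2 × (101·100·99·98·97)/(202·201·200·199·198) = 2 × 0.0297 = 0.059, not significant.
- a = 6: 2 × 0.0297 × 96/197 = 2 × 0.0145 = 0.029, significant.

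So at least 6 vs 0 is needed, an observed rate of 6/101 = 5.9% against none. The uncorrected chi-square needs at least 4 vs 0.

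**Step 2: power.** The chance of a significant result is the sum, over all tables (a, b) with p ≤ 0.05, of Bin(a; 101, p1) × Bin(b; 101, p2). Exact enumeration gives:

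| Assumed true rates | Fisher | Uncorrected chi-square |
|---|---|---|
| 0.1% vs 1% | 0.05% | 1.7% |
| 1% vs 2% | 0.6% | 5.7% |
| 1% vs 3% | 3.5% | 14.4% |
| 1% vs 5% | 19.8% | 37.5% |
| 2% vs 6% | 17.4% | 27.9% |
| 1% vs 10% | 77.5% | 85.8% |

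At 1% an arm of 101 yields about one event, so a twofold or threefold excess is almost invisible to Fisher's test. A tenfold excess is nearly always missed if it is 0.1% vs 1%, and usually found if it is 1% vs 10%.

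**Step 3: what an interval would add.** Take 5 vs 1 events. The Fisher p-value is 0.21. The proportions are 5/101 = 4.95% and 1/101 = 0.99%, a difference of 3.96 points. The Wilson 95% limits are 2.13% to 11.07% and 0.17% to 5.40%. Newcombe's method then gives

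- lower: 3.96 − √[(4.95 − 2.13)² + (5.40 − 0.99)²] = 3.96 − 5.23 = −1.3 points
- upper: 3.96 + √[(11.07 − 4.95)² + (0.99 − 0.17)²] = 3.96 + 6.17 = +10.1 points

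The p-value alone reports no significant difference. The interval shows that an excess of up to about 10 points is not excluded. Other splits by the same method:

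- 0 vs 0: −3.7 to +3.7 points
- 1 vs 0: −2.8 to +5.4 points
- 3 vs 1: −2.8 to +7.4 points (Fisher p = 0.62)

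The interval and the test can disagree near the boundary. For 5 vs 0, Newcombe gives +0.3 to +11.1 points while Fisher gives p = 0.059. This is a reason to name one method in advance as the basis of the comparison.

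**The case against.** The strongest case against the point has five parts.

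- **Per-arm figures are already planned.** This is correct. A reader might infer that safety rests on p-values alone, but {20a} promises counts and proportions for each group and item. A 5 vs 1 imbalance would be visible, and a risk difference could be derived from it. What is missing is a planned between-group estimate with its uncertainty.
- **No inference of equal safety is written down.** Also correct. A reader might infer that the investigators intend to treat p > 0.05 as proof of comparable safety. No section says so, and none sets a decision rule for safety. The misreading is a risk, not a stated plan.
- **Safety is not the formal objective.** Objectives {7} names efficacy only, Trial design {8} calls the trial exploratory, and safety is not among the listed primary or secondary outcomes. Low power for uncommon events is normal in a trial sized on efficacy. This stands, so the point asks for no safety margin, safety power or larger sample. It does not remove the promise to compare safety made in the abstract and the Discussion.
- **Interval methods are analysis-plan detail.** In part. Had the article been silent on the safety comparison, there would be no finding. It does fix a method, however, and that method suits the expected data poorly. Fisher's test is itself valid for sparse tables; the difficulty is how little a non-significant result conveys.
- **The size of the problem depends on assumed rates.** Correct. A reader might infer that a non-significant result is close to certain whatever the truth. That fails for large contrasts: 1% vs 10% is detected 77% of the time. Nor is it right to cut the arms to the 91 that allow for dropout, because the safety population keeps everyone with at least one dose.

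**Conclusion.** The point holds in a limited form. The one between-group safety comparison named in {20a} has little power at the rates the protocol's own wording suggests. For Fisher's test at 101 per arm, power is below 4% for 1% vs 2% or 1% vs 3%, and about 20% for 1% vs 5%. A non-significant result would therefore not support the safety comparison announced in the abstract and the Discussion.

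This rests on assumed event rates, because the protocol gives none. If real rates are higher and differ widely, the test works tolerably. The documents do not support saying that the plan will declare the drops equally safe, or that Fisher's test is the wrong test for sparse counts. The primary endpoint and the trial size are unaffected. This is an inexpensive improvement to the safety analysis.

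**What to change.** In Statistical methods {20a}, change the safety sentence to this effect:

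> In the safety population, the number and proportion of participants with any ocular adverse event, and with each listed event, will be given by arm. The arms will be compared by the risk difference (DQS minus HA) with a two-sided 95% confidence interval by Newcombe's method. Any p-values are descriptive. A non-significant result will not be taken as evidence of equal safety.

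An exact interval would serve equally well; one method should be chosen and named. Where an arm has no events, the interval still shows what is not excluded: 0 vs 0 gives −3.7 to +3.7 points.

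The change takes a few sentences and some extra table columns, with no new patients or data. The price is wide intervals, as in the 5 vs 1 example, and so a more cautious safety statement. The interval shows which excess risks remain possible; it does not decide which excess would be acceptable.

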#### Interim analyses {6}

There will be no planned interim analyses for this study. Since there are no anticipated problems that are detrimental to the participant, so interim analysis is not warranted.

#### Methods for additional analyses (e.g., subgroup analyses) {20b}

Subgroup analyses are not planned for this study.

#### Methods in analysis to handle protocol non-adherence and any statistical methods to handle missing data {20c}

We will use intention-to-treat analysis to analyze the data. Participants who do not follow the protocol are nevertheless considered for the analysis. Missing values will be handled using the best imputation method available.

#### Plans to give access to the full protocol, participant-level data, and statistical code {31c}

The datasets analyzed during the current study and statistical code are available from the corresponding author on reasonable request, as is the full protocol.

### Oversight and monitoring

#### Composition of the coordinating center and trial steering committee {5d}

The subject leader and the project manager will form the Steering Committee (SC). The SC accountable for managing the whole project and having ultimate authority for the study. The SC will write and submit the report for publication at the end of the study.

The Monitor Group’s (MG) inspectors are appointed by the SC. The MG will oversee the entire research procedure in compliance with the GCP requirements. The inspector analyzes the investigator’s adherence to the protocol, the protection of participants’ rights and interests, the quality of the case report form (CRF), and the investigators’ understanding of different standards before submitting inspection reports to the SC.

The principal investigator designated a person (HESH, Department of Clinical Research) to be in charge of the data management. This study uses the Electronic case report form and management tool to collect data.

#### Composition of the data monitoring committee, its role, and reporting structure {21a}

The Department of Clinical Research in HESH to be in charge of the data management The database will be constructed using Excel (Microsoft, USA 2022 version), and regular data monitoring will be undertaken in accordance with the sponsor’s standard operating procedures. The SC manages the trial under the supervision of the MG.

#### Adverse event reporting and harms {22}

Due to the low-risk nature of the trial, no AEs are anticipated. For very rare cases such as eye secretion, eye irritation, eye itching, congestion, and eye pain, HESH Certified Review Board will be notified; experimental treatments will be discontinued promptly, and professional ophthalmologist will provide treatment .

#### Frequency and plans for auditing trial conduct {23}

The trial will be conducted and monitored by the principal investigator. The steering committee will meet weekly to review and evaluate updates.

#### Plans for communicating important protocol amendments to relevant parties (e.g., trial participants, ethical committees) {25}

If there are modifications to eligibility criteria, outcomes, or analyses needed for the study, a revised protocol will be submitted for approval to the Medical Ethics Committee at HESH, Shenyang, China.

#### Dissemination plans {31a}

The study’s findings will be shared regardless of the effect’s direction. All possible beneficiaries of the research, including patients, carers, family, doctors, advisory boards, and medical boards, will receive trial data. Publications in high-impact, open-access medical journals and talks at national and international medical conferences will serve this purpose.

## Discussion

DM is a complex metabolic disorder and several mechanisms have been speculated for the cause of DE in DM patients. Some suggest that insulin is necessary for the proliferation of acinar lacrimal gland and cornea epithelial cells [30], while others propose that the tear reflex is weakened owing to diabetic corneal neuropathy-induced corneal insensitivity [31]. Additionally, it has been shown that the amount of glucose and advanced glycation end-products (AGEs) might rise in tears, promoting hyperosmolarity and inflammation [32].

Prior studies have shown that DM increases the risk of developing chronic DED [33, 34] due to tear protein alteration, decreased corneal sensitivity, and lower reflex-induced tear secretion [35]. Manaviat et al. [36] observed that the prevalence of DED in type 2 diabetic patients was 54.3% and that the rate of morbidity was significantly greater than in non-diabetic controls. In addition, they discovered that DED was substantially linked with age, gender, diabetes duration, and diabetic retinopathy. Studies conducted by Najafi et al. [37] and Zou et al. [34] suggest that glycosylated hemoglobin (HbA1c) levels had an association with diabetic DED.

DQS stimulates P2Y2 receptors on the ocular surface, which enhances the secretion of water and secretory mucin from conjunctival tissue. Therefore, tear film stability and quality can be improved [38]. However, the effect of DQS on the tear film of DM humans has not been previously assessed. This result should allow us to compare the clinical efficacy and safety of 3% DQS in diabetic patients with DED and provide clinicians with more treatment options. On the other hand, HA is a glycosaminoglycan, and with its sponge-like structure of polysaccharide chains, it can bind with water and acts as a reservoir for slowly releasing water molecules [39]. As a result, HA eye drops are commonly used to treat DED, while initial findings from a pilot study suggest that HA eye drops can improve signs and symptoms of diabetic DE [40]. The possible benefits exhibited by the two topical ophthalmic eyedrops will be related to corneal epithelial recovery and secretion and not changes in the underlying pathology created due to DM.

However, a large RCT has not been conducted to understand the benefits of HA eye drops on diabetic DED patients.

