Around 0.1% hyaluronic acid (HA) used in artificial tears has been reported to promote corneal re-epithelium and improve corneal healing [11]. Additionally, HA has been reported to decrease the rate of tear evaporation and enhance the stability of tear film [12]. HA ophthalmic drops have emerged as a first-line treatment of choice for dry eye disease (DED) [13].

Although the significance of DED related to DM has been acknowledged and however, no clear guidelines for treatment options have been established or recommended [14]. Both DQS and HA eye drops are often prescribed to DED sufferers and are found to be clinically effective. However, these studies did not focus on evaluating the effectiveness of different eye-drop treatments in individuals with DED related to DM.

Therefore, the purpose is to assess and compare the effectiveness of DQS and HA topical eye drops on DM-related DED.

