##### Control arm (active control)

Participants will utilize HA eyedrops as it has been shown to stimulate tear and mucus production on the ocular surface as a first-line treatment of choice for DED.

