#### Intervention description {11a}

In this study, patients will receive either DQS (Diquas; Santen Pharmaceutical Co., Ltd., Osaka, Japan) or 0.1% hyaluronic acid (HA) artificial tears (preservative-free) eye drops for 8 weeks based on their randomized group allocation. The dosage for both drugs is 1 drop, 6 times per day. Two follow-up visits were performed on day 28 (4 weeks) and day 56 (8 weeks) in week 8 in both groups, comprehensive eye exams will be conducted by an ophthalmologist including primary outcomes, secondary outcomes, and safety evaluation.

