### Sample size {14}

The sample size calculation is based on the primary outcome measures, named NITBUT, to establish the non-inferiority between the groups in terms of the changes in the mean from the baseline at day 56. For the NITBUT, a sample size of 164 subjects, 82 in each group, is sufficient to detect a clinically important difference of 5.24 s [26] between groups in reducing DED assuming a standard deviation of 5.23 s [27] using a two-tailed *t*-test of difference between means with a power of 80% and a level of significance of 5%. Considering a dropout rate of 10% the sample size required is 182 (91 per group). With an additional 10% compensation for the potential deviation of dry eye metrics from a normal distribution [26, 27], the sample size required is 202 (101 per group).

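### The sample size section sets a non-inferiority aim without a margin or any stated HA effect in diabetic dry eye, so similar arms could not show non-inferiority or that either drop works

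*Protocol article*

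**What the plan says.** All references are to the protocol article.

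- **Arms.** There are two, DQS and 0.1% HA, with no placebo, vehicle or untreated arm (Trial design {8}, Intervention description {11a}). HA is the active control, chosen "as a first-line treatment of choice for DED", that is, for dry eye in general.
- **Objective.** Objectives {7} asks for a comparison of the efficacy of DQS and HA. The Discussion paragraph of the abstract goes wider: "clinical trial designed to evaluate the therapeutic effects and safety of DQS and HA for diabetic dry eye treatment".
- **Hypothesis.** Sample size {14} aims "to establish the non-inferiority between the groups in terms of the changes in the mean from the baseline at day 56". The same paragraph computes the sample size from a two-tailed t-test, with a difference to detect of 5.24 s, SD 5.23 s, 80% power and 5% significance. It names no margin.
- **Analysis.** Section {20a} plans an ANCOVA on NITBUT with baseline as covariate (two-sided 5%, 95% CI) and paired t-tests within each group.
- **Evidence on HA in diabetic dry eye.** On earlier work with the two drops, the Background says "these studies did not focus on evaluating the effectiveness of different eye-drop treatments in individuals with DED related to DM". The main Discussion reports that "initial findings from a pilot study suggest that HA eye drops can improve signs and symptoms of diabetic DE", and then adds "However, a large RCT has not been conducted to understand the benefits of HA eye drops on diabetic DED patients".

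**The concern.** A non-inferiority conclusion borrows its meaning from the reference treatment. It shows that the new drop works only if the reference is known to work in the population studied, and if the margin is no larger than that known effect. The protocol names non-inferiority as the aim but supplies neither the margin nor the HA effect from which one could be derived, and its planned tests are tests of difference.

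At stake is how similar arms at day 56 would be read. Both drops may have helped, or neither may have, and two arms cannot separate these. Under the stated aim, a non-significant p-value could be reported as DQS being as good as a first-line drop. Under the abstract's wider wording, improvement within each arm could be reported as a therapeutic effect of both.

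**Working it through.** **1. The plan's own figure.** Inputs from Sample size {14}: difference 5.24 s, SD 5.23 s, two-sided 5% (z = 1.960), power 80% (z = 0.842).

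n per group = 2 × (1.960 + 0.842)² × (5.23 / 5.24)² = 2 × 7.85 × 0.996 ≈ 15.6, so 16 (17 by the exact t calculation).

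The stated 82 per group does not follow. Reading 5.24 s as a non-inferiority margin with a true difference of 0 (one-sided 2.5%) also gives 16, so that reading does not explain 82 either. At 82 per group, power for 5.24 s exceeds 99.99%. The later steps do follow: 164 / 0.9 = 182.2 and 182 / 0.9 = 202.2.

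**2. What 82 per group can resolve at SD 5.23 s.** Standard error of the difference = 5.23 × √(2/82) = 0.817 s.

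- 95% CI half-width = 1.960 × 0.817 = 1.60 s (1.44 s with 101 per group).
- Difference detectable with 80% power, which is also the margin that 82 per group would support at a true difference of 0: 2.802 × 0.817 = 2.29 s.

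These ignore any gain in precision from the baseline covariate.

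**3. A non-significant result is not non-inferiority.** An observed difference just under 1.60 s against DQS is non-significant, but its CI reaches 1.60 + 1.60 = 3.20 s worse. With identical observed means, the CI still runs from −1.60 to +1.60 s. Without a margin, nothing says which of these results would pass.

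**4. No margin can be derived from the document.** Let e be HA's true NITBUT effect over no treatment in diabetic dry eye, and m the margin. Passing non-inferiority shows only that DQS's effect over no treatment exceeds e − m. The protocol gives neither quantity, so the values below are assumptions to show the range (seconds):

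| Assumed e | m = 1 | m = 2 | m = 3 | m = 5.24 |
|---|---|---|---|---|
| 0 | −1 | −2 | −3 | −5.24 |
| 1 | 0 | −1 | −2 | −4.24 |
| 2 | +1 | 0 | −1 | −3.24 |
| 3 | +2 | +1 | 0 | −2.24 |

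Passing implies benefit only where e is at least m, and the document does not show where e lies. The margin also drives the size. At SD 5.23 s, one-sided 2.5% and 80% power, margins of 1, 1.5, 2 and 3 s need 430, 191, 108 and 48 evaluable participants per group.

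**5. The paired t-tests do not fill the gap.** They compare each arm with its own baseline and have no untreated control. NITBUT of 5 s or less is one of the entry criteria (Eligibility criteria {10}: two or more of three criteria are required). Some participants therefore enter on a low reading, and part of any rise may be regression to the mean.

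**The case against.** The strongest reply is that no non-inferiority test is planned. Objectives {7} is comparative, Trial design {8} calls the trial exploratory, and both the t-test in {14} and the ANCOVA in {20a} are two-sided tests of difference. On this view the word non-inferiority is a slip in one sentence, and the recommended comparison with a 95% CI is largely in place. A margin might also stand in a statistical analysis plan that is not shown, and a two-sided 95% CI could be read against it.

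Much of this stands. It limits the point to the stated aim and the claims built on it, and it makes the repair easy. It does not remove the conflict: the aim and the test that contradicts it are printed in the same paragraph. A margin set elsewhere would still need an HA effect in this population, and the evidence presented here is a pilot study with no figure.

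A reader might infer more than the document supports:

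- *The protocol concedes that HA's benefit is unestablished.* It does not. It says no large RCT exists, directly after citing a supportive pilot, and it calls HA first-line for dry eye in general.
- *HA is the wrong comparator, or the design cannot meet its objective.* An active comparator alone is a legitimate choice, and two arms can answer the head-to-head question in {7}.
- *The trial claims to fill the evidence gap on HA.* The Discussion names that gap but does not say this trial closes it.
- *5.24 s is the margin.* The text calls it a clinically important difference to detect. If it were used as a margin, DQS could be observed 5.24 − 1.60 = 3.64 s worse and still pass. That is an illustration, not the plan.
- *The mechanism given for HA under Control arm undermines the comparison.* It sits awkwardly with the Background and Discussion, but no endpoint, sample size or analysis depends on it.

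**Conclusion.** The point holds for the hypothesis and the claims, and not for the choice of comparator. Sample size {14} states a non-inferiority aim that has no margin, does not match the planned two-sided tests, and has no HA effect in diabetic dry eye behind it. A result of no difference therefore cannot support non-inferiority to an effective drop, or the efficacy of either drop in this population, and the within-group tests cannot support it either. A significant between-arm difference remains interpretable as relative efficacy.

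In size: with 82 evaluable per group, a non-significant result is compatible with DQS being up to about 3.2 s worse. This assumes that the stated SD of 5.23 s applies to the day 56 comparison and that the baseline covariate gives no extra precision. How much of HA's effect any margin would preserve cannot be calculated from the document.

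**What to change.** 1. In Sample size {14}, replace the non-inferiority aim with a two-sided test of the between-arm difference in NITBUT change from baseline to day 56, reported with its 95% CI. This matches the t-test there and the ANCOVA in {20a}.
2. In the abstract's Discussion paragraph, limit the efficacy claim to the effect of DQS relative to HA. The safety wording can stay.
3. Add to {20a} that neither a non-significant difference nor a within-group change will be reported as non-inferiority or as evidence that either drop is effective in diabetic dry eye.

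Objectives {7} needs no change. The failure of 82 per group to follow from its inputs needs its own correction, which this rewording does not supply.

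Cost: wording only, with no added participants, arms or visits. It does change the stated hypothesis, and Trial status reports that recruitment began in May 2023. It should therefore go through the amendment route in section {25}, before the database is locked and the data are analysed. The sponsor gives up a claim that DQS is as good as first-line treatment if the arms turn out similar.
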